### Subjects

24 patients with pathologically confirmed prostate cancer, progressive disease, who have no active CNS metastases or vital organ compromise, ages 18 years of age and older, available for at least 41 weeks of follow-up from the time of screening.

Arm 1. 12 patients, receiving DC/LNCaP vaccine and the DC/LNCaP-M1 and DC/KLH immunizations over 8 weeks.

Arm 2. 12 patients in the placebo Arm for 8 weeks followed by DC/LNCAP vaccine and the DC/LNCaP-M1 and DC/KLH immunizations over 8 weeks.

#### Proposed enrollment

24 patients will be enrolled. Implementation of enrollment is contingent upon approval of the protocol and consent for by the Rockefeller University institutional review board (IRB). Candidates identified for study entry will have the details of the study carefully discussed, prior to asking the individual to read and sign the consent form. Patients choosing to enter the study will be randomized according to a randomization schedule provided by the Biostatistician.

#### Inclusion/exclusion criteria

Screening to determine eligibility (with the exception of HLA haplotyping) will be completed within 45 days of study entry.

##### --Disease Characteristics--

1. Histologically confirmed prostate carcinoma

2. Progressive, disease required, i.e.: elevated PSA documented to be rising on 3 occasions, either despite castrate testosterone levels (below 50 ng/dl), or after definitive local therapy (prostatectomy or radiation).

| Extent of disease | Min # of values | Interval |
| --- | --- | --- |
| Rising PSA within 2 years of prostatectomy | 3 | >2 weeks |
| Rising PSA post-radiation* | 3 | >2 weeks |
| Rising PSA despite castrate testosterone | 3 | >2 weeks |

*Baseline is defined as the first of three rising values confirmed after definitive radiation treatment.

3. No active CNS metastases

##### --Prior/Concurrent Therapy--

1. Recovered from toxicity of any prior therapy

2. Biologic therapy:

No prior autologous or allogeneic tumor vaccines

No concurrent other immunotherapy

3. Chemotherapy:

At least 4 weeks since chemotherapy

Not previously treated with more than 2 chemotherapy regimens

No concurrent chemotherapy

4. Endocrine evaluation/therapy:

3 rising PSA values at least 2 weeks apart

At least 2 weeks since concurrent corticosteroids (other than for replacement therapy for adrenal insufficiency)

Medical hormonal therapy to maintain castrate testosterone levels permitted

5. Radiotherapy:

At least 4 weeks since radiotherapy

No concurrent radiotherapy

6. Surgery:

Prior surgery allowed

##### --Patient Characteristics--

1. Age: 18 and over, able to give written informed consent. Individuals unable to provide informed consent must have consent provided by the legal guardian, or person designated by the subject to give consent on his behalf.

2. Performance status: Karnofsky 70-100%

3. Life expectancy: At least 1 year

4. Hematopoietic: obtained twice, once within 45 days prior to study entry, and again within 72 hours of study entry.

WBC greater than 3,800

Absolute neutrophils greater than 1,500

Absolute lymphocytes greater than 500

Platelets greater than 120,000

Hb at least 10 g/dl

5. Hepatic:

Bilirubin less than 2.0 mg/dl OR

SGOT less than 2 x ULN

6. Renal:

Creatinine no greater than 2.0 mg/dl OR

Creatinine clearance at least 40 ml/min

7. Rheumatologic:

ANA no greater than upper limit of normal, or ANA abnormal in absence of clinical signs of autoimmunity.

Rheumatoid factor (RF) no greater than upper limit of normal, or RF abnormal in absence of clinical signs of autoimmunity.

Anti-ds DNA no greater than upper limit of normal, or anti ds DNA abnormal in absence of clinical signs of autoimmunity.

1. Immunologic:

Influenza serology (assessment made at time of screening).

Assessment of DTH response to a tandard anergy panel (to include candida, trichophyton and tetanus) or to a Multitest CMI (a disposable kit for DTH testing with standardized preloaded antigens).

1. Cardiovascular:

No NYHA class III/IV status

No active angina, clinically significant cardiac arrythmia, recent (6 months) myocardial infarction

1. Pulmonary:

No severe debilitating pulmonary disease

1. Endocrine:

TSH, T3, and T4 no greater than upper limit of normal

1. Radiographic:

Baseline bone scan

Baseline CT or MRI of abdomen and pelvis

1. Other:

No active infection requiring antibiotics

No active pain requiring chronic opioid analgesics.

Not HIV, hepatitis B or hepatitis C virus positive; anti-HIV, HbsAg and Hep C antibody negative

No history of hypersensitivity to vaccine components

No serious uncontrolled medical illness

No currently active second malignancy other than non-melanoma skin cancer (note: a patient is NOT considered to have currently active malignancy if they have completed therapy and are now considered by their physician to be at less than 30% risk for relapse)

No history of total lymph node irradiation

No history of vasculitis, including but not limited to systemic necrotizing vasculitides (polyarteritis nodosa group), hypersensitivity vasculitis, Wegener’s granulomatosis.

No history of autoimmune disease.

No use of hydroxyurea within 45 days of study entry

No receipt of immune modulators or suppressors within 30 days prior to study entry, including but not limited to interferons and thalidomide. No active requirement for corticosteroids; prior use is acceptable.

No psychiatric illness or social condition that, in the opinion of the investigator, would interfere with adherence to study requirements.

No alcohol or drug use or dependence that, in the opinion of the investigator, would interfere with adherence to study requirements.

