##### Definitions for Schedule of Events

###### Screening. Screening will generally be completed within 45 days prior to study entry.

Medical History: The Principal Investigator or his designee will perform a thorough medical history.

Complete Physical Examination: The Principal Investigator or his designee will perform a complete physical exam at the indicated times.

Tests listed below will be conducted on samples collected and analyzed by standard procedures.

If any laboratory result is outside the reference range and is considered to be clinically relevant by the Investigator, the test will be repeated at appropriate time intervals until it returns to baseline or becomes a clinically insignificant finding.

Complete Blood Count: including differential white blood cell count, absolute neutrophil count, hemoglobin and platelet count.

Hematologic Tests: PT/PTT.

Blood Chemistries: Including total electrolytes (Na, K, Cl and bicarbonate, glucose, serum BUN and creatinine, alkaline phosphatase, and albumin.

Liver Function Tests: AST, ALT and total bilirubin.

Urinalysis: Including microscopic analysis.

Viral screens: HCV antibodies, Hepatitis B surface antigen, HIV antibodies, Influenza serology.

Rheumatologic screens: ANA, RF, dsDNA.

Thyroid screens: TSH, T3, T4.

HLA haplotype: complete HLA haplotype is obtained as part of the patient database, but is not used as a clinical screening parameter. Results of HLA haplotyping do not need to be available prior to leukapheresis at week 0.

Immunologic: DTH testing to standard anergy panel, including candida, tryichophyton and tetanus.

EKG

Radiologic Tests will be performed at Memorial Sloan-Kettering Cancer Center (preferably) or New York Weill Medical College. All tests will be read by a professional radiologist and compared with prior studies whenever these are available.

Chest X-Ray: Standard PA and lateral chest X-Ray, to be completed during screening, and, for follow-up imaging during the study, within 10 days of the dates indicated in the Schedule of Events.

Bone Scan: To be completed during screening, and, for follow-up imaging during the study, within 10 days of the dates indicated in the Schedule of Events.

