### Stopping rules

#### Criteria for Subject Study Discontinuation

- Development of an exclusionary condition as outlined in section (6)i.e.2, prior to or during vaccination, with the following exceptions:
  - a course of palliative radiation treatment during the study
- platelet counts that drop > 50% from baseline.
  - hemoglobin that drops sufficiently to require transfusion.
  - if the patient develops an infection requiring treatment as an inpatient.
- Failure by the subject to attend three consecutive clinical study visits.
- Request by the subject to withdraw.
- Clinical reasons judged by the study physician to be life threatening, even if not addressed in the toxicity management of the protocol.
- Completion of week 17 or in some patients, week 29 in Arm 1.
- Completion of week 25 or in some patients week 37 in Arm 2.
- Any dose limiting toxicity. A dose limiting toxicity is defined as:
  1. any grade 2 or greater allergic toxicity or asymptomatic bronchospasm or generalized urticiaria
  2. any grade 3 or greater toxicity (hematologic or non-hematologic)
  3. any grade 2 or greater autoimmune reactions

If a subject discontinues prior to completion of the study, the reason for and date of the discontinuation will be recorded. The date of the last dose of study vaccine will also be recorded. Subjects who discontinue prior to study completion may be replaced at the discretion of the Investigator.

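### The hepatic entry criterion joins its two limits with OR, so one passing liver test satisfies it however abnormal the other is, at odds with the stated population

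*Combined protocol and SAP*

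**What the plan says.** The hepatic item under Inclusion/exclusion criteria, Patient Characteristics, has two lines: "Bilirubin less than 2.0 mg/dl OR" and then "SGOT less than 2 x ULN". The next item, renal, has the same form and begins "Creatinine no greater than 2.0 mg/dl OR", with a creatinine clearance limit as the alternative.

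The Subjects section describes the 24 patients as men "who have no active CNS metastases or vital organ compromise". Indications to be studied and Estimated number of patients describe the population in the same terms.

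The screening panel in Definitions for Schedule of Events lists "Liver Function Tests: AST, ALT and total bilirubin". Data Accuracy and Protocol Compliance has the investigator or a designee check every inclusion and exclusion criterion before enrolment. Criteria for Subject Study Discontinuation then reuses the entry criteria: with listed exceptions, developing an exclusionary condition before or during vaccination ends participation.

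**The concern.** Bilirubin and SGOT are different tests, and a normal result on one does not make up for an abnormal result on the other. Joined by OR, the two limits leave the failing test uncapped. By way of illustration (these values are not in the documents), a man with bilirubin of 8 mg/dl and normal SGOT meets the hepatic criterion. So does a man with SGOT at 10 times the upper limit of normal and normal bilirubin.

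The protocol reports no earlier human use of the product, and its Objectives section makes safety primary. What is at stake is whether the written entry rule delivers the population the protocol says it will treat, and whether patients start with liver values against which an on-study change can be read.

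**Working it through.** No power, alpha or event count depends on this point, so the check is one of logic and of comparing sections.

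**Step 1: the rule as written.** Let A be bilirubin below 2.0 mg/dl and B be SGOT below twice the upper limit of normal. The criterion is A OR B.

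| Bilirubin limit | SGOT limit | A OR B | A AND B |
|---|---|---|---|
| met | met | satisfied | satisfied |
| met | failed, at any level | satisfied | not satisfied |
| failed, at any level | met | satisfied | not satisfied |
| failed | failed | not satisfied | not satisfied |

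The rule accepts 3 of the 4 combinations. Requiring both limits would accept 1 of 4.

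**Step 2: is the failing test capped elsewhere?** No. ALT is measured at screening but has no limit, and there is no second bilirubin or SGOT threshold. What remains is indirect: "No serious uncontrolled medical illness"; "Not HIV, hepatitis B or hepatitis C virus positive"; Karnofsky 70-100%; life expectancy of at least 1 year; recovery from the toxicity of earlier treatment; and the population description itself. None of these sets a liver-function limit.

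**Step 3: neighbouring criteria.** The five hematology limits are listed with no OR. The thyroid item requires all three of its tests to be within limits. The ANA, rheumatoid factor and anti-dsDNA items do accept an abnormal value, but only when there are no clinical signs of autoimmunity. The renal OR links two measures of one organ function. The hepatic item is the only one that accepts an unlimited abnormality in a separate test with no condition attached.

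**Step 4: carry-over to discontinuation.** The exclusionary hepatic condition is the negation of the entry rule: NOT (A OR B) = (NOT A) AND (NOT B). Both tests must fail. An isolated rise in one test therefore does not meet it. Separate triggers in the same list cover toxicity of grade 3 or higher, autoimmune reactions of grade 2 or higher, and reasons judged life threatening. What is left uncovered is an isolated rise beyond the entry limit, below grade 3, and not classed as an autoimmune reaction of grade 2 or higher. The width of that band cannot be given, because the cited toxicity criteria are not reproduced in the document.

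**The case against.** The strongest reply is that the hepatic line is one criterion among many. The Subjects section itself rules out vital organ compromise, so an investigator could turn away a visibly jaundiced man on that ground or for serious uncontrolled illness. The screening definitions also require an out-of-range result judged clinically relevant to be repeated until it resolves or is no longer significant. And the renal item uses the same OR, so the wording may be deliberate.

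Much of this stands. A reader might infer that a man with any degree of jaundice or transaminase elevation is eligible for the trial. The documents support only the narrower statement that he meets the hepatic criterion. But the remaining restraints depend on judgement, and an entry check against the listed criteria would pass him on the one line that puts numbers on liver function. The renal parallel leaves the intention open, but it does not make bilirubin and SGOT interchangeable.

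A reader might also infer that such a patient would count as a dose limiting toxicity and could stop the study at 1 of 3. The documents do not support this. It would mean treating an unchanged baseline value as a toxicity, whereas baseline signs and symptoms are recorded at week 0, adverse event collection concerns changes from baseline, and each event is given an attribution. It would also need toxicity grades that the document does not contain.

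**Conclusion.** The concern holds in this form. The hepatic criterion as written can be met with one liver test abnormal to any degree, no other numeric limit prevents this, and that contradicts the population described in three places. The conclusion rests on reading OR literally and on the absence of any other liver threshold in the document.

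The size is limited. Three of four is a count of logical combinations. The documents give no figure for how many candidates would have an isolated abnormality, so no number of patients can be attached. The 12 per arm, the 10% one-sided level and the stated power are unaffected. On study, it would be too strong to say that isolated rises go unaddressed: the gap is confined to those below grade 3 that no other trigger catches. The point still deserves correction, because the rule itself gives the wrong result in a first-in-human safety trial.

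**What to change.** Reconcile the hepatic line under Patient Characteristics with the population stated in Subjects, Indications to be studied and Estimated number of patients, so that the entry criterion enforces that population with the two limits already listed. If OR is intended, say so and give the reason. Because Criteria for Subject Study Discontinuation draws on the same criterion, the sponsor should also confirm what the hepatic line is meant to do there. That is a clinical decision for the sponsor, and this review does not propose a discontinuation rule.

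The cost is a change of one word, or one explanatory sentence, plus the confirmation. AST (the same enzyme as SGOT) and total bilirubin are already measured at screening, so no new test is needed. The downside is that a few patients with an isolated abnormality may become ineligible.

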##### Gender and Minority Inclusion

|  | American Indian or Alaskan Native | Asian or Pacific Islander | Black, not of Hispanic Origin | Hispanic | White, not of Hispanic Origin |
| --- | --- | --- | --- | --- | --- |
| Female | 0 | 0 | 0 | 0 | 0 |
| Male | 2 | 1 | 3 | 1 | 17 |
| Unknown | 0 | 0 | 0 | 0 | 0 |
| Total | 2 | 1 | 3 | 1 | 17 |

##### Participation of Children

Prostate cancer is not a disease of children. The age-specific mortality rate for invasive prostate cancer in the years 1992-1996 was 0/100,000 for individuals under age 34 (NCI SEER Cancer Statistics Review, 1973-1996). However, since rare instances may occur in young adults, the study will be open to eligible individuals age 18 or older.

### Vaccines

**DC/LNCAP:** Autologous dendritic cells that have been co-cultured with apoptotic LNCAP cells.

**DC/LNCAP-M1:** Autologous dendritic cells that have been co-cultured with apoptotic LNCAP-M1 cells that are stably transfected with a plasmid cDNA expressing the influenza matrix antigen.

**DC/KLH:** Autologous dendritic cells that have been exposed to KLH.

**Lot numbers**: 02-A1 to 03-A24

**Dose concentration**: 2-10 x 106 DC/LNCaP per injectate, 2-10 x 106 DC/LNCaP-M1 or 2-10 x 106 DC/KLH per injectate. Cells are resuspended in 0.5 ml 5% DMSO and 25% autologous serum in sterile saline for injection.

**Route of administration**: Cells will be injected into the subcutaneous tissue of the upper arm or thigh with a tuberculin syringe.

**Placebo**: either saline or vaccine vehicle only (5%DMSO in sterile saline.

### Study Design

Phase I/II prospective randomized, single-blinded, placebo-controlled trial with 2 arms describing the toxicity and activity of immunization with DC-LNCaP. Study participants in Arm 2, but not the investigator, study personnel, or those study participants in Arm 1 will be blinded with respect to up-front treatment (vaccine or placebo). At week 8, all patients will be made aware of which treatment arm they are in.

Arm 1. Subcutaneous injection of *ex vivo* generated autologous dendritic cells pulsed with apoptotic LNCaP cells, pulsed with apoptotic LNCaP-M1 cells (control apoptotic cells) and pulsed with KLH (control antigen). In addition, subcutaneous injection of either saline or vaccine vehicle only (5% DMSO in normal saline ).

Arm 2. Subcutaneous injection of either saline or vaccine vehicle only (5% DMSO in normal saline ), followed by cross-over to Arm 1 design.

#### Dosing Plan

All prostate cancer patients will undergo two leukapheresis procedures, one prior to vaccination and a second 6 weeks after the final vaccination. Those in Arm 2 will undergo a third leukaphereesis, prior to the placebo phase. Their cells will be cryopreserved in aliquots and will serve as a source of (prevaccination or postvaccination) cells throughout the study and will reduce the number and volume of blood draws.

The study is divided into 2 Arms of 12 patients each.

Arm 1 will have autologous DCs generated from pre-vaccination leukapheresis cells. Laboratory manipulation of the cells will be done according to Good Laboratory Practice guidelines. Cells will be co-cultured with apoptotic LNCaP or LNCaP-M1 tumor cells for an average of 36 hours (range 30-48 hours) prior to immunization. Vaccinations will occur on weeks 1, 3, 5 and 7. On weeks 1 and 3 patients will also be immunized with mature DCs exposed to KLH. For each subject, the maximal number of available DC will be re-injected with an anticipated range of 2 x 106 to 10 x 106 cells, depending on cell availability, in 0.5 ml volume. Patients will also be injected with either saline or vaccine vehicle only (5% DMSOin normal saline) at weeks 1, 3, 5 and7.

Arm 2 will have placebo (either saline or vaccine vehicle only (5% DMSOin normal saline )) injected on week 1, 3, 5 and 7, and will then switch over to DC/LNCaP and DC/LNCaP-M1 immunization on weeks 9, 11, 13 and 15. On weeks 9 and 11 patients will also be immunized with mature DCs exposed to KLH. Patients will also be injected with either saline or vaccine vehicle only (5% DMSO in normal saline ) at weeks 9, 11, 13 and15.

#### Duration

Immunizations will be given over the course of 7 weeks. All patients will be followed to Week 17 (Arm 1) or Week 25 (Arm 2). The longest duration of follow-up will be blood draws 29 (Arm 1) or 37 (Arm 2) weeks after study entry in selected patients with either clinical or immunological responses or adverse events. Patients who have completed at least 13 weeks (Arm 1) or 21 weeks (Arm 2) of the study will be considered to have completed the study, although all patients will be encouraged to remain in the study for the full 17 (Arm 1) or 25 (Arm 2) weeks.

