Arm 2 (placebo followed by vaccine):

Weeks 1, 3, 5 and 7 Either saline or vaccine vehicle alone (5% DMSO in sterile saline) is given SQ in single injections of 500 l. At week 9, 11, 13, and 15 autologous DCs co-cultured with apoptotic irradiated LNCaP cells are given SQ in single injections of 500 l. At each of these latter times, autologous DCs co-cultured with apoptotic irradiated LNCaP-M1 cells, as well as either saline or vaccine vehicle alone (5% DMSOin normal saline ) are given SQ in single injections of 500 l. On weeks 9 and 11, autologous DCs exposed to KLH are also given SQ. The SQ injections may be given +/- 3 days from the scheduled visit, with the exception that the first injection, which will be given on day 8 (preferably) or day 9 after the patient completes leukapheresis.

Administration of Vaccine

The DC/LNCaP vaccine is given approximately 6-8 cm from the axilla in the inner aspect of the upper arm. The DC/LNCaP-M1 vaccine is given approximately 6-8 cm from the axilla in the inner aspect of the patients’ contralateral upper arm. The administration site is prepared with betadine and alcohol swabs. Injection is given with a 25-gauge needle by superficial SQ injection (not in the fatty part). DCs exposed to KLH and either saline or vaccine vehicle alone may be given in the anteromedial thigh approximately 12-24 cm distal to the inguinal ligament.

Immunologic Studies

DTH: DTH will be performed at the Rockefeller University GCRC, concurrent with each vaccination and at 2 weeks, 10 weeks and in some patients, at 22 weeks post last vaccination. DTH reactions will be read at the Rockefeller University GCRC between 40-48 hours after implantation. Results will be recorded on the CRF.

Lymphoproliferative responses, ELISPOT and CTL: Assays will be performed at the Rockefeller University.

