##### Activity

Activity of vaccination will be measure by monitoring both clinical and immunologic parameters. The primary clinical parameter of activity will be PSA measurement. Secondary clinical parameters include monitoring of measurable disease, assessed by chest X-Ray, bone scan and CT scan/MRI scans.

PSA will be measured in the MSKCC laboratory and serially monitored starting at the screening visit, Day 0, Week 3, 4, 5, 7, 9, 13, and 17, (and possibly 29) for participants in Arm 1 and on screening visit, Week 3, 4, 5, 6, 7, 9, 11, 12, 13, 15, 17, 21, and 25, (and possibly 37) for participants in Arm 2.

Complete response (CR): PSA < 4.0 ng/ml for 3 successive evaluations at least two weeks apart.

Partial Response (PR): Decrease in PSA value by > 50% (without normalization) for three successive evaluations at least two weeks apart.

Stabilization (SD): Patients who do not meet the criteria for PR or PD for at least 90 days on study (post vaccine; week 1 (Arm 1) or week 10 (Arm 2)).

Progression (PD): Three consecutive increase in PSA from baseline or nadir, each measurement at least two weeks apart.

Time to PSA Progression: The first PSA rise after the nadir PSA that is confirmed by two consecutive PSA at least two weeks or more apart.

Measurable disease

Patients will be evaluated at baseline, and at 5 weeks and 17 weeks after completion of therapy. Response and progression of measurable disease will be evaluated by bone scan and soft-tissue CT scan, using criteria proposed by the Response Evaluation Criteria in Solid Tumors (RECIST) Committee (Therasse et al., 2000). Changes in only the largest diameter (uni-dimensional measurement) of the tumor lesions are used in the RECIST criteria. Note: Lesions are either measurable or non-measurable using the criteria provided below.

Measurable disease: Defined as lesions that can be accurately measured in at least one dimension (longest diameter to be recorded) as >20 mm with conventional techniques (PET, CT, MRI, x-ray) or as >10 mm with spiral CT scan.

Non-measurable disease: All other lesions, including small lesions, are considered non-measurable disease. Bone lesions, leptomeningeal disease, ascites, plueral/pericardial effusions, lymphangitic disease, inflammatory disease are all non-measurable.

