### Monitoring and follow-up.

Patients will be monitored intensively at the Rockefeller University Hospital following each vaccination. Patients will be monitored directly for one hour after each vaccination. Patients may stay longer or may be admitted as necessary or at the discretion of the PI. Antihistamines and epinephrine will be available for treatment, as appropriate, of any allergic reactions. The local injection site and draining lymph nodes will be monitored for inflammation and swelling. Patients receiving placebo will not receive DTH tests (other than saline), so as not to tolerize them to subsequent vaccination.

Possible local reactions that should be recorded include erythema and induration (measured using a flexible ruler and pain/tenderness, or warmth at the injection site). Local or systemic reactions will be noted on the case report forms.

In the event of a local or systemic reaction, patients will be monitored until the reaction has resolved. All grade 3 or more severe reactions will require immediate notification of a study physician. Monitoring will include direct supervision by nursing and physician staff, monitoring of vital signs and physical examination as needed, and other appropriate medical measures as deemed necessary.

During the week after each immunization, the subject will be examined or contacted by phone by the investigator or his designee to obtain local and systemic reaction data and to determine the subject’s clinical status. Instructions to subjects leaving the Rockefeller University GCRC post-vaccination will include directions and telephone numbers to use in the event of any unusual or severe sign or symptoms. Subjects reporting such symptoms should be seen in the Rockefeller University GCRC at the time of maximal symptoms, and will be followed up clinically until resolution of symptoms.

Interim outpatient visits will include history and physical examinations as well as monitoring of clinical laboratory studies, as detailed in the schedule of events. Between outpatient visits, for the first 7 days post immunization, a self-assessment questionnaire will be completed by the patient with instructions to notify the study team by phone if any systemic symptoms or unusual or severe symptoms are experienced.

Longer term follow up will be performed at graded intervals following vaccination (weeks 9, 13, 17 and possibly 29 in Arm 1, and weeks 17, 21, 25 and possibly 37 in Arm 2).

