#### Analysis of immunogenicity data.

Immunogenicity data will be tabulated and quantitated for each of the quantitative assays planned. These include proliferation assays, ELISPOT assays, and CTL assays. For example, we will correlate positive or negative responses (proliferation index > 5, ELISPOT T cell responses > 100 SFC/106 T cells, and CTL responses with % specific killing > 15%) with positive or negative responses to our positive control antigens (influenza M1) and, where available, to the prostate antigens PSMA and PAP.

For ELISPOT, CTL response, LPA and DTH, the primary analysis will be based on the change from baseline. Changes in baseline will be summarized by the median and 25th and 75th percentiles, and arms compared with the Wilcoxon rank sum test. Additionally, the longitudinal responses will be examined using generalized estimating equation analyses (to incorporate all the responses on a subject).

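### The week 29/37 samples come only from patients selected for response or adverse event, but the additional longitudinal GEE takes in every response, so its late time course is biased in a direction the plan leaves open

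*Combined protocol and SAP*

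**What the plan says.** Under *Study Design – Duration*, all patients are followed to week 17 in Arm 1 or week 25 in Arm 2. Later follow-up is limited to "blood draws 29 (Arm 1) or 37 (Arm 2) weeks after study entry in selected patients with either clinical or immunological responses or adverse events". Other sections agree that the late visit is not for everyone:

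- *Monitoring and follow-up* lists "weeks 9, 13, 17 and possibly 29 in Arm 1, and weeks 17, 21, 25 and possibly 37 in Arm 2".
- *On-study evaluations* (Immunologic Studies) schedules DTH after vaccination "at 2 weeks, 10 weeks and in some patients, at 22 weeks post last vaccination". The last vaccinations are at weeks 7 and 15, so 7 + 22 = 29 and 15 + 22 = 37: this is the same late visit.

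*Analysis of immunogenicity data* covers ELISPOT, CTL, LPA and DTH. The primary analysis is change from baseline, with arms compared by the Wilcoxon rank sum test and no visit named. In addition, "the longitudinal responses will be examined using generalized estimating equation analyses (to incorporate all the responses on a subject". No working correlation, mean model, visit set, weighting or missing-data rule is given, and nothing excludes the week 29/37 values.

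**The concern.** Immunological response is one of the stated reasons for taking a late sample, so the presence of a week 29/37 value depends on earlier values of the outcome being modelled. An unweighted GEE is generally valid only when missing values are unrelated to outcome. Here the late mean rests on a selected group and is set against a week 17/25 mean from everyone.

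This is bias in the estimate itself, and robust standard errors do not repair it. DTH is the primary immunogenicity parameter and is explicitly measured at this visit. At stake is any statement, drawn from the longitudinal model, about how immune responses behave after week 17/25.

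**Working it through.** The plan states no figure for the longitudinal analysis, so there is nothing to reproduce. The check is an illustration.

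**Inputs from the protocol:** 12 patients per arm; weeks 9, 13 and 17 for all in Arm 1, week 29 for some; ELISPOT positive above 100 SFC per million T cells.

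**Assumed, not in the documents:** 4 of 12 patients respond at 200 SFC and 8 sit at 20 SFC; SD 20; means flat to week 17; responders halve by week 29 and the others stay at 20; patients above 100 SFC are resampled.

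**1. True change.** Week 17 mean = (4 × 200 + 8 × 20)/12 = 960/12 = 80. Week 29 mean = (4 × 100 + 8 × 20)/12 = 560/12 = 46.7. Change = 46.7 − 80 = −33.3.

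**2. Independence working correlation, visit means.** The week 29 mean is that of the sampled patients, 100. Apparent change = 100 − 80 = +20. Simulation gives about +20.

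**3. As step 2, with 30% of patients also sampled for adverse events, unrelated to response.** Expected extra non-responders = 0.3 × 8 = 2.4. Late mean = (4 × 100 + 2.4 × 20)/(4 + 2.4) = 448/6.4 = 70. Apparent change = 70 − 80 = −10. Simulation gives about −9.

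**4. Exchangeable working correlation on weeks 9, 13, 17 and 29.** Differences between patients dominate, so the estimated correlation is close to 1. The model then in effect gives the unsampled patients the sampled patients' own change, 100 − 200 = −100. Simulation gives about −104, roughly three times the true fall.

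**5. Responders keep 75% instead of 50%.** Week 29 mean = (4 × 150 + 8 × 20)/12 = 760/12 = 63.3, so the true change is 63.3 − 80 = −16.7. Independence: 150 − 80 = +70 (simulated 69 to 71). Exchangeable: 150 − 200 = −50 (simulated about −53).

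| Analysis, 50% retained | Week 29 minus week 17 (SFC) |
|---|---|
| Truth | about −33 |
| Independence, responders sampled | about +20 |
| Independence, plus 30% sampled for adverse events | about −9 |
| Exchangeable, four visits | about −104 |

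**6. A second set of assumptions.** 24 patients; mean changes from baseline of 1.0, 0.8, 0.6 and 0.3 SD at weeks 9, 13, 17 and 29; within-patient correlation 0.3 to 0.7; the highest 25% to 50% of earlier responders sampled late. True week 29 minus week 17 is 0.3 − 0.6 = −0.30.

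- Independence, visit means: −0.05 to +0.62.
- Independence, one linear slope: mainly flattened, −0.005 to −0.22 per 10 weeks against a true −0.34.
- Exchangeable, correctly specified, with selection only on the modelled assay: −0.28 to −0.36, so the decline is recovered.
- Correct correlation, but 33% of patients selected on a variable outside the model that is related to the underlying response: −0.06 to −0.24, so waning is understated.

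**The case against.** The strongest reply is that the plan does not commit to the model that does the damage. A correctly specified exchangeable GEE, with selection only on the modelled assay, recovers the decline (step 6). That stands as a limit on the claim, but it does not clear the plan. No correlation structure is named, selection also uses clinical response and adverse events, which are not stated to be in the model, and in the SFC illustration the exchangeable fit exaggerates the fall.

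Second, adverse-event sampling dilutes the selection. The protocol expects injection-site reactions and sets no grade for this criterion, so that route could be wide. This stands: it moves the independence result from about +20 to about −9. It shrinks the bias without removing it.

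Third, only DTH is explicitly placed at the late visit. That ELISPOT, CTL and LPA are run on that blood is an inference, since Table 2 is not available in the text. This stands, and the SFC figures are illustrative for that reason too.

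Fourth, following responders longer is a legitimate exploratory choice, and the GEE is additional. This also stands; the criticism is of pooling, not of taking the samples.

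A reader might infer three stronger things that the documents do not support:

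- *That a waning response will be reported as rising.* This happens under some specifications only; others flatten or exaggerate the fall.
- *That a durability objective is compromised.* The *Objectives* section speaks of evaluating immunogenicity from baseline and post-immunization responses, and states no aim about the late time course.
- *That time to PSA progression is biased.* PSA at the late visit is indeed optional ("Week 3, 4, 5, 7, 9, 13, and 17, (and possibly 29) for participants in Arm 1"), but *Data analysis* plans no analysis of time to PSA progression and no bias in it has been shown.

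**Conclusion.** The concern holds as a bias of unspecified size and direction in the late part of an additional analysis. The selection rule and the intention to use all responses are both explicit, and nothing in the plan keeps the selected visit out of the model or corrects for it.

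Under the assumed values the same true change of about −33 SFC could be reported as anything from about +20 to about −104, depending on working correlation and breadth of adverse-event sampling. Those figures rest wholly on the assumed response levels, retention and selection, and show sensitivity rather than a forecast.

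The primary Wilcoxon analysis is affected only if its unnamed visit is week 29/37. The pre-crossover PSA comparison and the safety comparison are not affected. The point deserves a change because the remedy is cheap, not because a primary conclusion is threatened.

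**What to change.** In *Analysis of immunogenicity data*, limit the GEE to visits scheduled for all patients: through week 17 in Arm 1 and week 25 in Arm 2. Report week 29/37 values separately, as each selected patient's paired change from his own week 17/25 value, labelled as coming from patients selected for response or adverse event. In the illustration that summary would show the sampled responders' own fall of about 100 SFC, which is correct for them and makes no claim about the arm.

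If an all-patient summary of time to PSA progression is ever produced, cut it off at week 17/25 as well.

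The cost is wording only. No visit is added and no sample is discarded. The GEE loses the few late samples, which are still reported descriptively.
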